### Study objectives and outcome

The primary objective is:

The efficacy of nonavalent HPV vaccination in women with a CIN II-III lesion who underwent a LEEP in preventing recurrent CIN II-III after at 24 months follow-up.

The secondary objectives are:
The recurrence of CIN I-II-III at 6, 12 and 24 months.The effect of HPV vaccination on HPV DNA presence at 6 and 24 months after LEEP.The effect of HPV vaccination on Pap-smear results.Number of LEEP for recurrent CIN.Cost-effectiveness analysis from a societal perspective: intramural and extramural medical costs questionnaire (iMCQ) and productivity cost questionnaire (iPCQ) will be performed at the start of the study, at 2 months and after 24 months.Quality of life will be assessed with quality of life questionnaire: Euroqol 5D-5 L at the start of the study, at 2 months, at 6 months and after 24 months.Side effects and adverse events. One week after each vaccination, a telephonic interview will be performed to ask for side effects after the injection.

The tertiary and long-term objectives are:
Cytology result after 5 years by retrieving HPV-test and Pap smear results from the national database of the population based cervical cancer screening program.Cytology result after 10 years by retrieving HPV-test and Pap smear results from the national database of the population based cervical cancer screening program.Vaccination effect on premature delivery and obstetrical complications by comparing the results to a national database on childbirth data.

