**Fig. 2 Fig2:**
[figure not shown]
Schedule of enrolment, interventions, and assessments VACCIN-study. * Follow up is according to national guideline, when needed cytology, HPV typing or colposcopy is performed and data is collected between 6 and 24 months. ** When result at 24 months is either HPV positive or ≥ PAP2 a colposcopy is performed

1 week follow-up:
Side effects of the injection, Result of LEEP (no CIN, CIN I, II or III) and LEEP margins (clear margins or CIN in margins).

2 months follow up:
Side effects of the injection.QoL (Euroqol 5D-5 L) and societal economical costs questionnaire (iPCQ, adjusted iMCQ).

6 months follow-up:
Cytology results and HPV genotype, QoL (Euroqol 5D-5 L) questionnaire.Side effects of the injection.

24 month follow-up:
Cytology results and HPV genotype. When either test is abnormal, colposcopy will be performed and biopsies taken for histologic study endpoint.QoL and societal economical costs questionnaire (iPCQ, adjusted iMCQ).All other cytology test, colposcopy results, LEEP result and HPV genotype test between appointment 6 months and 24 months follow-up if appropriate.Pregnancy during follow-up with obstetrical outcome.

60 and 120 months follow-up:
Collection of HPV test and Pap smear result via population screening program and sub sequential treatment.Collection of national database on childbirth data on subsequent pregnancies and the following pregnancy outcomes: gestational age, miscarriages, preterm rupture of membranes.

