### Statistical analysis

The main analysis for the primary outcome testing the hypothesis of superiority of nonavalent vaccine as compared to placebo, for preventing CIN II-III recurrence after 24 months will be conducted using a χ^2^ test. Outcome measure for the primary outcome is a relative risk with 95% confidence interval.

Relative risks will also be estimated for secondary categorical outcomes, with 95% confidence intervals and χ^2^ or Fisher’s exact test for significance. Continuous data will be described using means with standard deviation, or medians with interquartile ranges; t-tests or Mann-Whitney U tests will be used as appropriate. Kaplan-Meier curves will be made for time between LEEP, vaccination with active or placebo and CIN II-III recurrence. The curves will be compared using the log-rank test. Quality of Life will be measured at every visit. They will be assessed with Euroqol 5D-5 L questionnaire. Patients from both groups will be analyzed using generalized linear mixed models.

The cost-effectiveness will be assessed by calculating the incremental cost-effectiveness ratio (ICER), defined as the difference in costs, divided by the average change in effectiveness of the vaccine versus a placebo following LEEP treatment. A Budget impact analysis (BIA) will be performed, in accordance with the principles for good practice for BIA, to address the financial stream of consequences in order to assess the affordability of offering the vaccine following LEEP treatment. BIA will compare the likely impact of replacing LEEP by HPV vaccination on national health plan budgets, on hospital level and on assurance level. From the viewpoint of the government, the broad societal perspective and the ‘budgetary framework for care’ will be highlighted. A valid framework (Markov model) will give insight into the budget consequences. We will also perform sensitivity analyses and a ‘most optimistic versus pessimistic’ scenario. If the vaccine has a preventive effect, it will be included in the new national guideline. As a result, the health care insurance can compensate this as regular care.

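### No cost questionnaire between months 2 and 24 puts the societal cost difference at risk, because productivity loss and care outside the hospital have no other listed source in that period

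*Protocol article*

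**What the plan says.** Under Study objectives and outcome, the economic objective reads "Cost-effectiveness analysis from a societal perspective: intramural and extramural medical costs questionnaire (iMCQ) and productivity cost questionnaire (iPCQ"), and these questionnaires "will be performed at the start of the study, at 2 months and after 24 months". The visit list under Data collection agrees. At 2 months it has "QoL (Euroqol 5D-5 L) and societal economical costs questionnaire (iPCQ, adjusted iMCQ"), the same questionnaires return at 24 months, and the 6-month entry is limited to "Cytology results and HPV genotype, QoL (Euroqol 5D-5 L) questionnaire" plus injection side effects. No recall period is given for either instrument.

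Clinical events have a separate source. The 24-month entry collects "All other cytology test, colposcopy results, LEEP result and HPV genotype test between appointment 6 months and 24 months follow-up if appropriate", the note to Fig. 2 says that "when needed cytology, HPV typing or colposcopy is performed and data is collected between 6 and 24 months", and one secondary objective is "Number of LEEP for recurrent CIN".

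Statistical analysis gives the ICER as "defined as the difference in costs, divided by the average change in effectiveness of the vaccine versus a placebo following LEEP treatment". It does not say how vaccine price, vaccine administration or placebo injection visits enter the costs.

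**The concern.** A societal analysis has to count work loss and care outside the hospital as well as hospital procedures. The arms should differ in these costs mainly when recurrences are found and managed, and that work falls largely between the 6-month test and month 24. No cost questionnaire is given in that stretch. Because the schedule is stated twice and consistently, it is a design choice in the text and not a detail left to a fuller document.

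At stake is the cost difference in the ICER, which Statistical analysis places beside the budget impact analysis and the prospect of guideline inclusion and insurance cover. Productivity and extramural data that are not collected as the trial runs cannot be reliably recovered afterwards.

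**Working it through.** **Inputs**
- Cost questionnaires at start, 2 and 24 months; EQ-5D-5L also at 6 months (Study objectives and outcome; Data collection).
- Second dose at least 1 month after the first, third at least 3 months after the second (Interventions).
- Recurrence at two years 3% on vaccine and 8% on placebo; 750 women (Sample size calculations), allocated 1:1 (Randomisation, blinding and treatment allocation).
- Recall period R at month 24: not stated, so varied below as an assumption.

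**The plan's own figure.** No unit cost, cost difference or ICER is stated, so there is none to reproduce. The recurrence rates are those behind the stated 646 patients. With two-sided alpha 0.05 (sidedness assumed), power 0.80 and unpooled variance, n per arm = (1.960 + 0.842)² × (0.08 × 0.92 + 0.03 × 0.97) / 0.05², just over 322. Rounded up this is 323, or 646 in total. The sample size is not in question here.

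**Gap.** 24 − 2 = 22 months. The third dose comes at the earliest 1 + 3 = 4 months after the first, so it lies inside the gap.

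**Coverage.** Uncovered months between 2 and 24 = 22 − R. Uncovered months between 6 and 24 = 18 − R, not below zero. Expected recurrences per arm of 375: 375 × 0.08 = 30 on placebo and 375 × 0.03 = 11.25 on vaccine, before attrition. Spreading them evenly over months 6 to 24 (an assumption) gives the number outside any questionnaire window:

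| R (months, assumed) | Months 2–24 uncovered | Share of months 6–24 uncovered | Placebo recurrences outside | Vaccine recurrences outside |
|---|---|---|---|---|
| 1 | 21 of 22 (95%) | 17/18 = 94% | 28.3 | 10.6 |
| 3 | 19 of 22 (86%) | 15/18 = 83% | 25.0 | 9.4 |
| 6 | 16 of 22 (73%) | 12/18 = 67% | 20.0 | 7.5 |
| 12 | 10 of 22 (45%) | 6/18 = 33% | 10.0 | 3.8 |
| 22 | 0 | 0 | 0 | 0 |

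**Effect on the cost difference.** Let c be the productivity and extramural cost of one recurrence (not given). The saving missed per woman is (0.08 − 0.03) × share uncovered × c. With R = 3 this is 0.05 × 0.83 × c = 0.042c; with R = 12 it is 0.05 × 0.33 × c = 0.017c. If effectiveness is taken as recurrences averted, dividing by 0.05 overstates the ICER by 0.83c or 0.33c from this source alone.

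**Effect of added questionnaires.** One at 6 months looks back over months 2 to 6 and still leaves 24 − 6 = 18 months, the period when recurrences are managed. Questionnaires at 6 and 12 months give intervals of 4, 6 and 12 months, so the longest recall needed falls from 22 to 12 months.

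**The case against.** The strongest reply is that the costly events are already recorded. Cytology, HPV tests, colposcopies and LEEPs between 6 and 24 months are collected apart from the questionnaires, and repeat LEEPs are a secondary outcome. This stands. A reader might infer that recurrence procedures depend on 22-month recall, or that the ICER will be wrong; the documents support neither. What remains is productivity loss and extramural care.

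A second reply is that the recall period is unstated and the iMCQ is described as adjusted, so the last questionnaire might reach back to month 2. That is possible, and the uncovered share would then be zero. But those costs would rest on recall of up to 22 months. A shorter recall leaves months unmeasured, so the schedule is weak on either reading.

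A third issue is the comparator. Placebo women attend for the same three injections, so a reader might infer that these visits cancel the vaccine's delivery cost, at 3 / 0.05 = 60 visits per recurrence averted, or 2 / 0.05 = 40 if the first dose is given on the LEEP day. This happens only if placebo visits are costed as incurred, which Statistical analysis does not say. With placebo visits costed at zero, there is no such bias. A costing rule of this kind is commonly left to the full protocol or economic plan, so it is a clarification to request and not an error.

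Finally, this is a secondary objective: the primary outcome and its test are untouched.

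**Conclusion.** The point holds for productivity and extramural costs. The stated schedule leaves 22 of 24 months between cost questionnaires, and no other listed source covers these two components there. Under the assumed recall periods, the uncovered part of months 2 to 24 runs from 95% (1 month) to none (22 months), with 86% at 3 months and 45% at 12 months. The recurrence counts also assume the planned 8% and 3% and an even spread over months 6 to 24.

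The direction of this component is clear: recurrence costs that go unmeasured are larger on placebo, so the vaccine's savings are understated. A reader might go on to infer a direction for the whole ICER. The documents do not support that. No unit costs are given, and if placebo visits were costed as incurred, that would pull the other way. The cost difference is at risk of bias; neither the size nor the net sign of an error in the ICER can be established.

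**What to change.** 1. Add the electronic iMCQ and iPCQ at 6 months, alongside the EQ-5D-5L already given there, and at least once more between 6 and 24 months, for example at 12 months. The 6-month addition alone is not enough.
2. State the recall period of each questionnaire and match it to the interval since the previous one.
3. State that cytology, HPV tests, colposcopies and LEEPs are costed from eCRF counts and unit prices, not from patient recall.
4. As a secondary clarification under Statistical analysis, state that placebo injection visits and time are excluded from comparator costs, and that vaccine price and administration are included in the vaccine arm. The decision to be informed is vaccine plus LEEP against LEEP alone.

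The cost is a small extra questionnaire burden for participants, set-up in the existing electronic system and some wording. Clinical care, the sample size and the primary analysis do not change.

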## Abstract

**Background:**

Cervical cancer is caused by Human Papilloma viruses (HPV) and is preceded by precursor stages: Cervical Intraepithelial Neoplasia (CIN). CIN is mostly found in women in their reproductive age and treated with a Loop Electrosurgical Excision Procedure (LEEP). The recurrence or residual disease rate after treatment is up to 17%. These women have a lifelong increased risk of recurrent CIN, cervical cancer and other HPV related malignancies. Furthermore, LEEP treatments are associated with complications such as premature birth. Limited data show that prophylactic HPV vaccination at the time of LEEP reduces recurrence rates, therefore leading to a reduction in repeated surgical interventions and side effect like preterm birth.

The primary study objective is to evaluate the efficacy of the nonavalent HPV vaccination in women with a CIN II-III (high-grade squamous intraepithelial lesion (HSIL) lesion who will undergo a LEEP in preventing recurrent CIN II-III after 24 months.

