## Background

Worldwide, cervical cancer is diagnosed annually in more than 500,000 women and is still a major health problem among women worldwide [1]. Cervical cancer is preceded by Cervical Intraepithelial Neoplasia (CIN) of the cervix and caused by high risk Human Papilloma Viruses (hrHPV) [2]. CIN is subdivided in three groups: CIN I mild dysplasia, also known as low grade squamous intraepithelial lesion (LSIL). CIN II is mild dysplasia and CIN III severe dysplasia, both also known as high-grade squamous intraepithelial lesion (HSIL). Persistent hrHPV infection is a prerequisite to develop cervical cancer. About 80% of women will be infected with HPV during their life and most women are able to clear the HPV infections. However, approximately 20% of these women have detectable transient infections and a fraction will subsequently develop to cervical cancer if not treated for these precursor lesions [3]. With adequate screening and treatment of CIN, cervical cancer can be prevented [4].

The most commonly used method to treat CIN II-III is Loop Electrosurgical Excision Procedure (LEEP) to prevent possible progression to invasive cancer. Data on recurrent disease after LEEP vary in the literature. Up to 17% of women treated for CIN II-III have residual or may develop recurrent CIN II-III [5, 6]. Treatment is associated with side effects such as hemorrhage, infection, and stenosis of the cervix, and as well as adverse pregnancy outcomes, such as premature rupture of membranes and premature birth. Re-excision is needed in case of recurrence with an increased risk for adverse events. Especially the adverse obstetrical outcomes are higher after multiple treatments [7–9]. Women treated for CIN also have an increased risk of developing cervical, vaginal and vulvar cancer compared to patients with normal primary smear test results [10–12]. To prevent HPV-related diseases, eradication is preferable to treating recurrences repeatedly [13]. Recurrence can be monitored by HPV testing.

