### In- and exclusion criteria

Women are eligible for participation if they are eighteen years old or above, histologically proven CIN II or III and will be treated with a LEEP. Inclusion must be within four weeks after LEEP. Exclusion criteria are: a prior HPV vaccination, invasive carcinoma, immune-compromised women, pregnant women, prior treatment for CIN-lesions, insufficient understanding of the Dutch language or allergic to vaccine components.

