### Randomisation, blinding and treatment allocation

Randomisation will be performed through the secure web-based interface Castor EDC (Castor Electronic Data Capture, available at: https://castoredc.com). Patients will be randomised to either active study medication, or placebo in a 1:1 ratio. Randomisation will be stratified by age, categorized as being 18 to 29 years, 30 to 44 years, or 45 years and older. Women aged 18 to 29 years are not eligible for routine screening under the national screening program. The second stratum includes women of 30 to 44 years who are of reproductive age and invited for routine testing under the national screening program. The third stratum women of 45 years and older, who are less likely to be fertile. Randomisation will use random permuted blocks of sizes 2 and 4.

Both doctor and patient will be blinded for treatment allocation. The allocated medication will be prepared and distributed by the hospital pharmacy as syringes with identical appearance.

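### The vaccination effect on premature delivery is defined by a comparison with a national childbirth database, which cannot separate the vaccine from LEEP and CIN; it should be vaccine versus placebo

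*Protocol article*

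**What the plan says.** Under Study objectives and outcome, the last tertiary and long-term objective is: "Vaccination effect on premature delivery and obstetrical complications by comparing the results to a national database on childbirth data". It names both the quantity wanted (an effect of vaccination) and the way to get it (a comparison with the database).

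The list under Data collection uses the database differently. At 60 and 120 months it plans: "Collection of national database on childbirth data on subsequent pregnancies and the following pregnancy outcomes: gestational age, miscarriages, preterm rupture of membranes". At 24 months it plans to record: "Pregnancy during follow-up with obstetrical outcome". Neither entry names a comparator, and neither is limited to one arm.

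The Statistical analysis section assigns tests to the primary and secondary outcomes and does not mention the obstetric objective.

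Three other statements bear on the point:
- Eligibility requires "histologically proven CIN II or III and will be treated with a LEEP", so both arms have the index LEEP.
- The Abstract says that "LEEP treatments are associated with complications such as premature birth", and the Background adds: "Especially the adverse obstetrical outcomes are higher after multiple treatments".
- On allocation: "Patients will be randomised to either active study medication, or placebo in a 1:1 ratio".

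**The concern.** A contrast estimates a vaccination effect only if the groups compared differ in vaccination and in little else. Women in the trial differ from women in a national birth register in at least two further respects, CIN II-III and LEEP. The article says that the second of these goes with premature birth. The placebo arm shares both features with the vaccine arm, but it is not named as the comparator.

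Two errors could follow if the objective is carried out as worded. A vaccine with no obstetric effect could appear harmful, because the excess risk after LEEP would be read as a vaccine effect. A real benefit, such as one gained through fewer repeat excisions, could be hidden by the same excess. Preterm birth is part of the trial's stated rationale, so readers will look for this result although it is tertiary.

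**Working it through.** The article gives no figure for this objective, so there is none to reproduce. It gives no preterm rate, number of pregnancies or size of LEEP effect. All values for these below are assumptions.

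**1. What the stated comparison returns.** Let *k* be the ratio of preterm risk in LEEP-treated women with CIN on placebo to the national risk, and *r* the true vaccine risk ratio. The wording leaves open which results are compared with the database.

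| Results set against the database | Quantity obtained | Value if the vaccine does nothing (*r* = 1) |
|---|---|---|
| Vaccine arm only | *k* × *r* | *k* |
| Both arms pooled, equal numbers of pregnancies | *k* × (1 + *r*)/2 | *k* |
| Each arm separately | *k* × *r* and *k* | *k* and *k* |

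No entry equals *r* unless *k* = 1. In the third row *r* is recovered only by dividing one result by the other: (*k* × *r*)/*k* = *r*. That is the vaccine-versus-placebo comparison, and the national rate cancels out of it.

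**2. Size, under assumption.** Take *k* from 1.3 to 2.0. With *r* = 1 the vaccine arm against the database gives 1.3 to 2.0, whatever the national rate. Vaccine against placebo gives 1.0. For the database comparison merely to look neutral, *r* would have to be 1/1.3 = 0.77 to 1/2.0 = 0.50.

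**3. A benefit through avoided repeat LEEP.** The Sample size calculations section assumes recurrence of 3% with vaccine and 8% with placebo. Suppose every recurrence leads to a second LEEP before the pregnancy, and that a second LEEP multiplies preterm risk by *q* (assumed 1.5 to 3). Then

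*r* = (0.97 + 0.03*q*)/(0.92 + 0.08*q*)

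- *q* = 1.5: 1.015/1.040 = 0.976
- *q* = 2: 1.030/1.080 = 0.954
- *q* = 3: 1.060/1.160 = 0.914

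On these assumptions the benefit by this route is a reduction of about 2% to 9%. An assumed LEEP and CIN excess of 30% to 100% would swamp it.

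**4. What the randomised comparison can deliver.** With *m* pregnancies per arm and preterm risk *p*, the standard error of the log risk ratio at RR = 1 is √[2(1 − *p*)/(*mp*)].

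- *m* = 30, *p* = 0.07: √(1.86/2.1) = 0.941, so the 95% interval around 1 is 0.16 to 6.33. Power for RR 0.5 is about 9%.
- *m* = 150, *p* = 0.11: √(1.78/16.5) = 0.328, so the interval is 0.53 to 1.90. Power for RR 0.5 is about 41%.

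The between-arm estimate targets the right quantity but would be imprecise across this range.

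**5. The two places side by side.** The objective makes the database the thing compared with. The 60- and 120-month entry makes it the place from which participants' outcomes are taken. The two cytology objectives just before it also use a national database to retrieve participants' results. The obstetric objective alone uses a database as a comparator.

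**The case against.** The strongest reply is that this is loose wording about a data source. The neighbouring objectives and the Data collection list point that way. The end of the Background sets vaccine against placebo as the comparison for the trial as a whole. The article also condenses a fuller protocol, and a tertiary linkage analysis 5 to 10 years out is often specified elsewhere. The objective does not say which women in the database would serve as reference, or whether they would be matched or adjusted.

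Much of this stands as a limit on the point. A reader might infer that the sponsor means to discard the randomised control arm. The article does not support that: nowhere does it say that placebo pregnancies are left out, and obstetric data are collected without restriction by arm. A reader might also take 1.3 to 2.0 as the expected bias. It is not: *k* is assumed and comes back by construction, so it shows direction and mechanism only. If the reference women were selected for CIN and LEEP, *k* could be nearer 1, but the article describes no such selection.

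Nor is the between-arm comparison of pregnancies free of difficulty. Preterm delivery is seen only in women who conceive after randomisation, so that analysis conditions on a post-randomisation event.

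What does not stand is the claim that nothing needs correcting. The comparator is stated, so this is not a detail left to another document. If the database was meant as a data source, the objective misdescribes the method. If it was meant as comparator, the method cannot give the stated effect. Both readings call for the same change.

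**Conclusion.** The point holds as an error in a stated method. As worded, the objective cannot estimate a vaccination effect on premature delivery or obstetrical complications, because the named comparator differs from the participants in LEEP and CIN as well as in vaccination. It also disagrees with the Data collection list on what the database is for.

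The direction, towards apparent harm, follows from the article's own link between LEEP and premature birth, provided the reference is national births not selected for CIN or LEEP. The size cannot be known from the article.

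The consequence is confined to a tertiary objective. The primary outcome, sample size, randomisation and blinding are untouched. The correction is still worth making, because a comparator that shares the index LEEP and the CIN history is already in the trial.

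**What to change.** Reword the tertiary objective along these lines: *Effect of vaccination on premature delivery and obstetrical complications, vaccine versus placebo as randomised, with outcomes in both arms obtained by linkage to the national childbirth database. National rates are shown as descriptive context only.* Align the 60- and 120-month entry under Data collection with this.

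Add two sentences of caution. First, an analysis limited to women who become pregnant conditions on a post-randomisation event; reporting events per randomised woman alongside it would help. Second, the estimate will be imprecise and should be presented with its confidence interval and without a claim of adequate power.

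The cost is wording only. The planned data collection is not restricted by arm, so no new data and no change in sample size are needed.
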